### Ethical approval

The institutional ethics review board was consulted and concluded that approval was not needed according to the Dutch law (letter CMO 6th April 2011). Patients will be asked to sign informed consent.

## Discussion

In this study, we will investigate whether GPs can be trained to more consistently pay attention to work aspects of health problems and to adopt a pro-active consultation style. We will also investigate whether this increases work-related self-efficacy in their patients. At this moment health problems that are related to work often linger on for a long time and can result in presenteeism and absenteeism without them being addressed properly by health professionals. We hypothesize that if GPs broaden their scope to include the working environment of their patients, more problems will be recognized in a phase in which it is easier to find solutions.

### Strengths and weaknesses of the study

An important strength of our study is the tailored character of the intervention that is based on the findings of our own focus group research. The training is expected to change the behaviour of GPs by making them more aware of the relationship between work, health and gender. This will enable them to recognize WRP in an earlier stage and this will also help them to use more effective therapeutic strategies.

In many trials regarding work related health problems, interventions aim at reducing sick leave. However a risk of taking sick leave as an outcome measure lies in it defining sick leave as the main problem rather than the conditions and circumstances that it is a result of. By our focus on work per se, including its important positive effects on health and well being, we think we can help GPs to better appreciate the meaning of work for patients. Using the beneficial effects of participation may be better suited to the preferences of GPs and the position of trust they have with their patients than playing a role in sickness certification. Once they acknowledge the important positive influence they can exert in this field for their patients, GPs may be motivated to further take up this task.

Another strength lies in the outcome measures we use. Currently, the registration by GPs of patients’ occupations and work related problems is inadequate. Even motivated GPs often do not know the relevant ICPC codes. This leaves much room for improvement making it more likely to find a significant effect of our intervention. Such an effect will also be relevant as registration of work related problems unequivocally shows that GPs pay attention to work. Improving the registration in the EMR has been subject of a government policy. Incentives are used to motivate GPs for adequate ICPC coding in the EMR. This may further stimulate GPs to use the ICPC codes for work related problems. The use of the RTW-SE scale in a primary health care setting will shed new light on the work-health relation of workers visiting their GP. Even if we do not find any effect on this scale, our data may be invaluable in further developing knowledge about the relationship between return-to-work self efficacy, absenteeism and presenteeism. Moreover, it will offer us insight in the possibilities of this instrument in a primary care setting, for instance as a diagnostic tool.

A weakness at patient level is the fact that most of the data are collected by self-reported questionnaires. This method is always subject to recall bias. However, since both the intervention- and control group will experience this bias, we do not expect that it will influence the comparison between the groups. Another weakness concerns the selection of patients. Only patients who are willing to participate are included This means our findings may not be transferable to all working patients. This effect is expected to occur in comparable ways in both groups.

A weakness at the GP level is the selection of GPs who are willing to participate. We assume that these GPs will be more open to new ideas and more positive concerning work-related issues. This may result in a smaller effect as there will be less room for improvement in the selected group. On the other hand, implementation of the programme amongst GPs in general is assumed to lead to a smaller effect. Heterogeneity of the group of GPs may be another problem. As work gets little attention during the vocational training and in quality improvement schemes of GPs, no ‘standard’ way of dealing with it has evolved. Therefore we expect to find a considerable inter-GP variation which, in its turn, can make it harder to reliably assess the effect of the training intervention.

We think that our study can mean an important step forward in health professionals paying more attention to work. This can lead to more effective and efficient health care for workers.

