## Methods

### Trial design

The study is a cluster randomised controlled trial using randomisation on practice level to prevent contamination. We will randomise the practices into two groups with a 1:1 allocation ratio. GPs in the intervention group practices will receive the training program, GPs in the control practices will deliver care as usual.

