### Randomisation

We aim to recruit at least 24 GPs who will be randomised into an intervention group and a control group. To prevent contamination, we will randomise clusters on practice level. A statistician will generate a block randomisation scheme using a block size of 2 and practices will be assigned to either condition according to the order in which they are recruited. After this order is established the allocation of the random sequence will be performed by the researcher.

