### Procedures

Inclusion will take place during a 4 month period, starting after the training of the intervention group GPs. The GPs’ receptionists will approach patients in the waiting room with a short questionnaire about age, number of working hours and their willingness to participate in the project. If a patient meets the selection criteria and signs informed consent the patient will be included and receive the first questionnaire. A second and third questionnaire will follow after 6 and 12 months. Forty patients for each participating GP, 20 females and 20 males, will be included for the study.

Only the intervention group GPs will be asked to fill in a form for each consenting patient with questions about: 1 the occupation of the patient; 2 the work relatedness of the problem that he/she presented; 3 whether sick leave was discussed; 4 whether the GP had suggested contacting an OP; 5 whether the GP had stimulated the patient to adopt a pro-active coping style. Two final questions asked whether the GP thought the training had been helpful for the consultation and if the GP had enough time for the consultation.

The control group will deliver care as usual. As it could be surmised that their usual care is influenced by the data collection we try to make sure that the data collection in the control group practices is carried out as much as possible by the receptionists supported by a research assistant. When data collection is completed the control group GPs are offered the same training as the intervention group as an incentive for adherence to the study protocol.

Patients will be approached by the receptionist before the consultation and, if they are prepared to participate in the study, are asked to answer the first questionnaire after the consultation and a second and third questionnaire after six and twelve months respectively.

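### Patients are enrolled after allocation, with trial tasks around inclusion that differ by arm, so comparable selection for the questionnaire outcomes is assumed rather than secured

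*Protocol article*

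**What the plan says.** All references are to the protocol article.

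- **Allocation.** Trial design: "We will randomise the practices into two groups with a 1:1 allocation ratio". Randomisation: "practices will be assigned to either condition according to the order in which they are recruited".
- **Timing of enrolment.** Procedures: "Inclusion will take place during a 4 month period, starting after the training of the intervention group GPs".
- **Who invites, and how.** Procedures: "The GPs’ receptionists will approach patients in the waiting room with a short questionnaire about age, number of working hours and their willingness to participate". This happens before the consultation and is described once, for both arms. The target is 40 patients per GP, half of each sex. No rule on consecutive approach is given.
- **What differs by arm.** Procedures: "Only the intervention group GPs will be asked to fill in a form for each consenting patient". In control practices, data collection is to be "carried out as much as possible by the receptionists supported by a research assistant"; no such support is described for intervention practices. Under Intervention, the last item of the GP training is instruction on data collection for the trial.
- **First measurement.** Procedures: the first questionnaire is answered after the consultation.
- **The claim.** Strengths and weaknesses of the study notes that only willing patients enter and that this may limit transferability, then adds: "This effect is expected to occur in comparable ways in both groups".

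**The concern.** Randomising practices balances, in expectation, the practices and their patient lists. It does not balance a patient sample drawn from those lists once the allocation is in force. If willingness to enrol, or readiness to invite, depends even slightly on arm, the two samples can differ before any effect of training.

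The article sees selection only as a question of transferability and assumes it is equal between arms. Its own procedures give reasons for doubt. Each enrolment adds a form for the GP in one arm only, and recruitment and data collection are not described as supported in the same way. Procedures already recognises that data collection could influence care in control practices and arranges their work accordingly, but the discussion of selection does not take that asymmetry into account.

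At stake is the RTW-SE comparison, the only patient-level primary outcome and the basis of the sample size. Such a shift could favour or disfavour the training, and recruiting more patients would not remove it.

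**Working it through.** **1. The plan's own figure.** Inputs from Sample size: SD 1.14, target difference 0.5 SD (0.57 points), alpha 0.05 (two-sided assumed, as sidedness is not stated), power 80%, intracluster correlation 0.15, 40 recruited and 30 analysed patients per GP.

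- Without clustering: 2 × (1.96 + 0.842)² / 0.5² = 62.8, so 63 per arm.
- Design effect: 1 + (30 − 1) × 0.15 = 5.35.
- GPs per arm: 63 × 5.35 / 30 = 11.2, rounded up to 12. Loss: 40 × 0.75 = 30.

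The stated 12 GPs per arm reproduces and is not in dispute.

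**2. Precision of the RTW-SE comparison.** With 12 × 30 = 360 patients analysed per arm, SE = √(2 × 5.35 / 360) = 0.172 SD, or 0.172 × 1.14 = 0.197 points. Power by the normal approximation is 83%.

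**3. Scale of a selection shift (assumed inputs).** The article gives no figure for this. Suppose that the share of enrolled patients with a work-related problem differs between arms by 5 to 20 percentage points, and that such patients score 0.5 to 1.0 SD lower. Shift b = difference in share × score gap.

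False-positive rate with no true effect: 1 − Φ(1.96 − b/SE) + Φ(−1.96 − b/SE). Power if the shift opposes a true 0.5 SD effect: Φ((0.5 − b)/SE − 1.96).

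| Share gap × score gap | b (SD) | b (points) | False-positive rate | Power if opposed |
|---|---|---|---|---|
| none | 0 | 0 | 5.0% | 83% |
| 0.05 × 0.5 | 0.025 | 0.03 | 5.2% | 79% |
| 0.05 × 1.0 | 0.05 | 0.06 | 6.0% | 74% |
| 0.20 × 0.5 | 0.10 | 0.11 | 8.9% | 64% |
| 0.20 × 1.0 | 0.20 | 0.23 | 21% | 41% |

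**4. Can the design detect the shift?** Not from RTW-SE. The first score is taken after contact with the trained or untrained GP, so a difference at that point may be selection, early effect or both. Age and working hours on the waiting-room form are recorded before the consultation and are free of this problem.

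**5. Which outcomes depend on enrolment?** Under Primary outcome measures, use of code Z05 is counted per GP and occupation registration is a percentage of the GP's working-age patients. Neither depends on who enrols. RTW-SE and the other patient-questionnaire outcomes do.

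**The case against.** The strongest reply is that the invitation is the same in both arms: same staff role, same place, same short form, same eligibility criteria, and before the consultation. The form does not ask about work problems. The GP form comes after consent, and the research-assistant sentence is about data collection in control practices and is meant to leave usual care undisturbed. It does not say that intervention practices lack such help. A journal article may also leave approach logs and covariate lists to the full protocol or analysis plan.

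Much of this stands, and it rules out several stronger readings that a reader might infer:

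- *That patients are invited by different procedures in each arm.* The documented differences lie in the tasks around inclusion. An effect on the invitation itself is inference.
- *That receptionists know the allocation.* The training is for GPs. The article does not say what receptionists know, nor that they are kept unaware.
- *That intervention practices will enrol more patients with work problems.* No mechanism is documented. The inputs in the illustration are assumptions, and only its extreme corner exceeds one standard error.
- *That the whole trial comparison is affected.* The two record-based primary outcomes are not.
- *That an RTW-SE score before the consultation would be of no use.* It would be the most direct covariate for the imbalance described, though not a complete cure. The plan does not collect one.

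What the reply does not supply is a reason to expect equal selection. A pre-consultation invitation lowers the risk but does not remove it when enrolment follows allocation, the quota leaves open who is approached, and each consent costs the GP extra work in one arm only. The point does not rest on omitted detail. It sets a stated expectation against stated procedures.

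**Conclusion.** The concern holds in limited form. Following the article as written leaves RTW-SE and the other questionnaire outcomes open to differential selection, and the statement that selection will be comparable is unsupported. The documents show a risk, not a bias that has occurred, and they give neither its direction nor its size. On the assumed inputs above it ranges from negligible (0.025 SD) to material (0.20 SD, just above the standard error of 0.17 SD and two fifths of the target effect). The sample size figure and the record-based primary outcomes are not called into question. The point merits a change because the change is cheap and RTW-SE is the only patient-level primary outcome.

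**What to change.** 1. In both arms, have receptionists approach consecutive eligible attenders before the consultation, with the same arm-neutral information, until each sex quota is filled. Use existing research-assistant support for recruitment in the same way in both arms.
2. Keep the waiting-room form for everyone approached. Report numbers approached, eligible and consenting by arm, with age and working hours.
3. Include age and working hours, recorded before the consultation, as covariates in the multilevel model for RTW-SE. This is a partial remedy only, since neither captures whether a patient has a work problem. Adding sex would do almost nothing against selection because the quota already fixes it.
4. Replace the sentence on comparable selection with an acknowledgement that enrolment after allocation may lead to different selection by arm. This alone would be editorial; items 1 and 2 do most of the work.

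Cost: forms already handed out are kept, one recruitment instruction is aligned, and two covariates are added. The downside is slightly more paperwork at reception.
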